### Outcome measures

#### Primary outcome

The diagnostic test performance of translabial 3D ultrasonography as compared to MR imaging in detecting levator defects.

#### Secondary outcomes

1. Measuring the inter-observer agreement in diagnosing and in grading levator defects with 3D ultrasonography.

2. Measuring the association between levator defects and recurrent POP after anterior repair.

3. Evaluating potential cost-effectiveness of introducing 3D ultrasonography for diagnosing levator defects in the work-up of patients with POP.

### Data collection

The data will be recorded in a web based registry. Participants receive a case number to treat their data anonymously and to blind the observers. The observers are also blinded to all ultrasonography, MR-imaging data and clinical data. The patient and the attending gynecologist will not be informed of the findings in the study until the study has been finished.

### Sample size consideration

Ultrasound studies describe a prevalence of 20-40% of levator defects in patients with POP [15,17]. One MRI study detected levator defects in 55% of the women with POP. Calculating a sample size for the diagnostic test characteristics is complicated by the fact that only a few studies have been published about reproducibility of 3D ultrasound and in this study no other test characteristics were given. Assuming a sensitivity and specificity of 90% of 3D ultrasound for diagnosing levator defects in a population of 120 women with POP, with a prevalence of levator ani defects of 40%, we will be able to estimate predictive values with an accuracy of 10% below or above the point estimate of positive predictive values and negative predictive values.

Including 120 patients yields at least 80% to demonstrate that inter-observer agreement is substantial (Kappa >= 0.61), using a 0.05 significance level in one-sided testing, while expecting a 40% prevalence of levator defects and anticipating a value of the kappa statistic of 0.78 or better. In order to be able to detect a difference in recurrence rate after anterior colporrhaphy of 25% or more (35% in women with a levator defect vs 10% in women without levator defect), with an alpha of 5% and a power of 80%, a population of 102 patients with at least POPQ stage II prolapse in the anterior compartment, of whom 41 (40%) women with a levator defect, will be sufficient.

We are aiming to include 140 patients in this study, taking into consideration 3% technical problems in performing 3D-ultrasonography or MR imaging, which can result in non-evaluable images, and a further safety margin of 10%.

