**Methods/Design:**

A multicentre cohort study will be performed in nine Dutch hospitals. 140 consecutive women with a POPQ stage 2 or more anterior vaginal wall prolapse, who are indicated for anterior colporapphy will be included. Patients undergoing additional prolapse procedures will also be included.

Prior to surgery, patients will undergo MR imaging and translabial 3D ultrasound examination of the pelvic floor. Patients will be asked to complete validated disease specific quality of life questionnaires before surgery and at six and twelve months after surgery. Pelvic examination will be performed at the same time points.

Assuming a sensitivity and specificity of 90% of 3D ultrasound for diagnosing levator defects in a population of 120 women with POP, with a prior probability of levator ani defects of 40%, we will be able to estimate predictive values with good accuracy (i.e. confidence limits of at most 10% below or above the point estimates of positive and negative predictive values).

Anticipating 3% unclassifiable diagnostic images because of technical reasons, and a further safety margin of 10% we plan to recruit 140 patients.

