### Statistical analysis

Accuracy of 3D ultrasonography for diagnosing levator defects will be expressed in terms of sensitivity, specificity, standardized predictive values and their 95% -confidence interval. For the calculation of 95%-confidence intervals the Wilson formula for proportions will be used. ROC analysis will be performed for the grading of the size of levator defects with 3D ultrasound. Inter-observer and intra-observer agreement of diagnosing levator defects with 3D ultrasound will be evaluated by means of Cohen's Kappa coefficient and intra class coefficient. Logistic regression will be performed to determine whether levator defects constitute an independent risk factor for recurrence after POP surgery.

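### The promised 10-point limits for the predictive values hold with a Wald interval but not with the planned Wilson interval: the lower limit for PPV is expected about 12 points below the estimate

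*Protocol article*

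**What the plan says.** The Sample size consideration section sets the planning values: "Assuming a sensitivity and specificity of 90% of 3D ultrasound for diagnosing levator defects in a population of 120 women with POP". It adds an assumed defect prevalence of 40%. From these it concludes that "we will be able to estimate predictive values with an accuracy of 10% below or above the point estimate of positive predictive values"; the same is claimed for the negative ones. It does not name the interval behind this statement.

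The abstract (Methods/Design) gives the same planning values and defines good accuracy as "confidence limits of at most 10% below or above the point estimates of positive and negative predictive values". Each limit is therefore measured from the point estimate, on each side.

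The Statistical analysis section then fixes the method: "For the calculation of 95%-confidence intervals the Wilson formula for proportions will be used". Among the reported quantities it lists "standardized predictive values and their 95% -confidence interval".

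On recruitment: "We are aiming to include 140 patients in this study", which allows for 3% technical failures and a further 10% safety margin.

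**The concern.** The Wilson interval is not symmetric about the estimate. For a proportion well above one half it reaches further down than up. A symmetric precision target can therefore be met by a Wald interval and missed on the lower side by the Wilson interval from the same data. The PPV is the exposed quantity, because it rests on only about 50 test-positive women.

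The precision statement is the only sample-size argument the article gives for the primary outcome, diagnostic accuracy; the other two calculations in the section serve secondary outcomes. The lower limit for PPV also bounds how often a positive ultrasound may be wrong. If the stated precision does not match the interval that will be reported, readers expect a tighter result than the design delivers.

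**Working it through.** **Inputs.** N = 120 evaluable, prevalence 40%, sensitivity = specificity = 90%, target 10 points on each side (Sample size consideration; abstract). Two-sided 95% Wilson interval (Statistical analysis), z = 1.96. I read 10% as percentage points. A relative reading would be stricter for PPV (10% of 85.7 is 8.6 points), and even the Wald interval would then miss.

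**Expected table.** There are 120 × 0.40 = 48 women with a defect and 72 without.
- True positives: 48 × 0.90 = 43.2. False negatives: 4.8.
- True negatives: 72 × 0.90 = 64.8. False positives: 7.2.
- PPV = 43.2 / 50.4 = 0.857. NPV = 64.8 / 69.6 = 0.931.

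**Reproducing the plan's figure.** The Wald half-width is z·√(p(1−p)/n).
- PPV: 1.96 × √(0.857 × 0.143 / 50.4) = 0.097.
- NPV: 1.96 × √(0.931 × 0.069 / 69.6) = 0.060.

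Both are below 0.10, so the statement reproduces with Wald. The smallest N for which the Wald half-width for PPV is at most 10 points is 112.

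**The same table by Wilson.** Centre = (p + z²/2n) / (1 + z²/n). Half-width = z·√(p(1−p)/n + z²/4n²) / (1 + z²/n).
- PPV, n = 50.4: centre = (0.8571 + 0.0381) / 1.0762 = 0.8319. Half-width = 1.96 × √(0.002430 + 0.000378) / 1.0762 = 0.0965. Limits 0.735 and 0.928.
- NPV, n = 69.6: centre = (0.9310 + 0.0276) / 1.0552 = 0.9085. Half-width = 1.96 × √(0.000923 + 0.000198) / 1.0552 = 0.0622. Limits 0.846 and 0.971.

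| N = 120 | Estimate | Wilson 95% limits | Points below | Points above | Within 10? |
|---|---|---|---|---|---|
| PPV | 85.7% | 73.5 to 92.8% | 12.2 | 7.1 | lower no, upper yes |
| NPV | 93.1% | 84.6 to 97.1% | 8.5 | 4.0 | both yes |

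With whole counts (43 of 50) the lower limit for PPV is again 12.2 points below. Two other asymmetric intervals agree: Clopper-Pearson 12.7 and logit 12.6 points below.

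**Does the recruitment margin cure it?** 140 × 0.97 × 0.90 = 122.2. With 122 evaluable women the lower limit for PPV is 12.1 points below the estimate, and with all 140 it is 11.1. About 169 evaluable women would be needed to bring it within 10 at the same planning values.

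**Spread around the expected value.** I simulated studies at the planning values with N = 120 and let the number of women with a defect vary. The distance below had a median of about 12.1 points and a 95th percentile of 14.0. Close to half the studies exceeded 12.2, so 12 points is a typical value and not a bound.

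**The case against.** The best defence is that the 10-point figure is a planning half-width. On that reading nothing fails: the Wald half-width for PPV is 9.7 points and the Wilson half-width is 9.6. Planning on a half-width and analysing with Wilson is common practice. This probably explains where the figure comes from, and it shows that the figure is no slip of calculation. It does not rescue the abstract, which bounds the limits below and above the point estimate and so does not describe an average of the two distances.

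A second defence stands in part. The analysis section speaks of standardised predictive values without defining them in this article. Assume this means prevalence fixed at 40%. A simple Wilson interval on 50.4 test-positives is then not the relevant calculation. The variance of the log odds of PPV becomes 0.1/43.2 + 0.9/7.2 = 0.127. A logit interval then puts the lower limit 10.8 points below the estimate, and a symmetric delta-method interval gives ±8.6. The miss shrinks to under 1 point or disappears.

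Three stronger readings are tempting, and the document does not support them.
- A reader might infer that the claim is false for PPV at any prevalence the article cites. The claim is conditional on 40%. The article also reports that "One MRI study detected levator defects in 55% of the women with POP"; at 55% and N = 120 the lower limit for PPV is 9.3 points below and passes, while NPV is then 11.1 below. At 20% PPV is 17.5 below. These figures show sensitivity to the assumption, not an error in the stated claim.
- A reader might infer that sensitivity also breaks the promise, since its Wilson limits at n = 48 are 78% to 96%, or 11.7 points below. No precision was promised for sensitivity.
- A reader might infer that 120, or 140, is left without justification. The figure of 120 also serves the kappa calculation, and three of the four promised limits are met.

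**Conclusion.** The point holds in a limited form. At the article's own planning values, and with the interval it fixes for the analysis, one of four promised limits is not delivered: the lower limit for PPV is expected 12.2 points below the estimate instead of at most 10, and 11.1 points below even with no losses from 140. The upper limit for PPV and both limits for NPV meet the claim. The cause is that the planning statement matches a Wald interval while the analysis uses Wilson.

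The shortfall is about 2 points. It changes neither the analysis nor the recruitment target, but the stated precision should be corrected. The conclusion assumes that the 10% means percentage points and that PPV is analysed as a simple proportion of test-positive women. If a prevalence-standardised estimator is meant, the size of the miss depends on how its interval is built.

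**What to change.** Keep 140 patients and the Wilson interval. In the abstract and in Sample size consideration, replace the 10% statement by wording such as: at the planning values with 120 evaluable women, the expected 95% Wilson interval is about 74% to 93% for a PPV of 86% and about 85% to 97% for an NPV of 93%; the lower limit for PPV is expected to lie about 12 points below the estimate. Word this as an expected value, not a maximum, because individual studies will fall on either side of it.

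If predictive values standardised to a fixed prevalence are what will be reported, say so and compute the restated figures for that estimator and its interval. Intervals for sensitivity, and for prevalences of 20% and 55%, would be useful context but are optional.

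The cost is an edit in two places and a slightly less favourable stated precision. No extra patients and no change of analysis are needed.

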### Economic evaluation

Potential cost-effectiveness of translabial 3D ultrasound in the diagnostic work-up of a patient with POP to diagnose levator defects in order to identify patients at risk for recurrence, and subsequent adjustments of the type of surgery, will be determined by comparing diagnostic strategies. The incremental costs-effectiveness ratio(s) will be expressed as the incremental costs per recurrence avoided. As only part of the data needed to estimate potential cost-effectiveness of the 3D ultrasound will be collected empirically, a decision analytic model will be constructed [22,23]. The comparative sensitivity, specificity and costs of 3D ultrasound versus MR imaging for the diagnostic work-up of patients with POP will explicitly be incorporated in the model. The cost analysis will be performed from a hospital perspective, according to Dutch guidelines and will be estimated from study entry to twelve months follow up [24].

### Statistical analysis

Accuracy of 3D ultrasonography for diagnosing levator defects will be expressed in terms of sensitivity, specificity, standardized predictive values and their 95% -confidence interval. For the calculation of 95%-confidence intervals the Wilson formula for proportions will be used. ROC analysis will be performed for the grading of the size of levator defects with 3D ultrasound. Inter-observer and intra-observer agreement of diagnosing levator defects with 3D ultrasound will be evaluated by means of Cohen's Kappa coefficient and intra class coefficient. Logistic regression will be performed to determine whether levator defects constitute an independent risk factor for recurrence after POP surgery.

### Time plan

Patient recruitment started in March 2010 and is planned to continue until June 2011. The follow-up period is 12 months and therefore will continue until June 2012.

This study is conducted in cooperation with several centers collaborating in the Dutch Urogynecology Research Consortium. Most participating hospitals have a research nurse, who contributes to the counseling of the patient and the web-based data collection.

### Knowledge transfer

The outcome of this study will be important for the debate on the value of 3D ultrasound of the pelvic floor in a patient with pelvic organ prolapse for detecting levator defects. If the diagnostic accuracy of 3D ultrasonography in diagnosing levator defects and the clinical relevance of levator defects in this study will be confirmed, further implementation into guidelines and training of urogynecologists and ultrasonographers will be taken care of. It is also important to inform gynecologists if this relevance cannot be confirmed, if only to prevent any treatment based on a technique that is not relevant or accurate enough. The results of this study will be presented at national and international scientific meetings, and will be published in international scientific journals.
